**STATISTICAL ANALYSES**

Incidence rates and their differences with 95% confidence intervals (CIs) for incident CRC, CRC-related mortality, and all-cause mortality will be calculated using Poisson regression. To account for competing risk, we will apply subdistribution hazard model to estimate hazard ratios (HRs) and 95% CIs, using time since index date as the underlying time scale. Cumulative incidence function will be applied to estimate the cumulative incidence of the primary and secondary outcomes.

We will calculate the number needed to treat (NNT)^12^ to avoid one event at 10-year since it is the most commonly used time period for CRC^13^.

**Secondary analyses**

Three secondary analyses will be conducted. First, to assess the relationship between continuous statin treatment and outcomes, we will apply an as-treated analysis where we further censor the follow-up at the end of the first treatment episode, in addition to the abovementioned censoring criteria. Second, to evaluate whether cumulative duration of statin use is associated with the outcomes, we will apply a nested case-control study in statin users. Using the method of incidence density sampling, for each case exposed to statin and with later studied outcomes, we will randomly select up to five statin users who did not develop the interested outcomes (controls). They will be individually matched on age at index date, gender, IBD subtype, IBD duration, and duration of follow-up. Conditional logistic regression will be used to estimate odds ratios (ORs) with 95% CIs. The cumulative duration of statin use will be assessed between first prescription and end of follow-up, and categorized into categories (30 days-<1 year (reference group), 1-<2 years, 2-<5 years, and ≥5 years cDDD). Trends in the dose-response association will be tested by using the duration strata as an independent variable in the model. Third, we will repeat the main analysis without accounting for competing risks.

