**METHOD**

**Data source, study design, and study population**

This cohort study will be based on the nationwide histopathology cohort, Epidemiology Strengthened by histoPathology Reports in Sweden (ESPRESSO)^1^, and several healthcare registers in Sweden. ESPRESSO^1^ contains data on GI-related biopsies from all 28 pathology departments in Sweden from 1965 to 2017. The Total Population Register^2^ contains details on birth, death, and migration, which was initiated in 1968. The Prescribed Drug Register^3^ collects information on medications dispensed at all pharmacies in Sweden since July 2005, including for example dispensing date, drug name, and a defined daily dose (DDD). The National Patient Register^4^ covers data on inpatient (since 1964) and outpatient (since 2001) specialist care with disease diagnoses and surgical procedures. The Cancer Register^5^ contains data from >96% of incident cancer cases since 1958. The Cause of Death Register^6^ contains information on >99% of death since 1952. The Swedish Longitudinal Integrated Database for Health Insurance and Labour Market Studies^7^ contains information on demographic and socioeconomic characteristics (e.g., education and county of residence).

The IBD patients will be identified as those with ≥ 1 biopsy indicating IBD in the ESPRESSO and ≥ 1 International Classification of Disease (ICD) code for IBD in the NPR (see **Table 1** for the definition of IBD subtypes)^8^. Such diagnostic approach yields a positive predictive value of 95%^9^.

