**Identification of statin users**

Statin use will be identified from the Prescribed Drug Register by the Anatomical Therapeutic Chemical (ATC) code C10AA, including lipophilic statins (simvastatin and atorvastatin) and hydrophilic statins (pravastatin and rosuvastatin) (see **Table 2** for ATC codes). Statin users will be identified as those aged ≥ 18 years and with a statin prescription for ≥30 cumulative DDD (cDDD) from July, 2006 or later. The date that an individual first attained a cDDD ≥ 30 for a statin will be defined as the index date for statin exposure. Individuals who had any statin prescription before July 2006, before IBD diagnosis or before the first attainment of cDDD ≥ 30 will be excluded from the analysis to ensure a new-user design. We will use the intention-to-treat analysis as the main analysis.

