**Identification of primary and secondary outcomes**

Follow-up will begin at index date until the first recorded date of incident CRC, proctocolectomy, emigration, death, or end of follow-up (Dec, 2019). A patient who had a colectomy but had an intact rectum will be considered at risk of rectal cancer until proctectomy (see **Table 2** for procedure codes). The primary outcome is incident CRC (see **Table 2** for ICD codes), while secondary outcomes are CRC-related mortality and all-cause mortality (see **Table 2** for ICD codes).

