**Subgroup analyses and sensitivity analyses**

We will assess whether the associations vary by the following factors: age at the index date (<60 or ≥60 years), sex, calendar period for IBD diagnosis (1969-1999 or 2000-2018), educational attainment (0-9, 10-12, ≥13 years, or “missing”), IBD subtype (CD or UC), age at IBD diagnosis (<50 or ≥50 years), duration of IBD (<10 or ≥10 years), type of statins initially treated, and type of CRC (colon cancer or rectal cancer).

Several sensitivity analyses will be conducted. First, we will construct a model in which covariates will adjusted as time-varying variables. Second, we will exclude individuals with a history of CVD before statin initiation. Third, we will discard the first year and then first two years of follow-up from the analysis. Fourth, we will evaluate the potential influence from unmeasured confounding by calculating E-values^14^. Finally, we will perform a negative control analysis using fracture as a negative control outcome to assess potential biases in our study^15^.

Data analyses will be performed using SAS version 9.4, Stata (version 16.1), and R version 3.6.0.

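### The as-treated analysis censors users at the end of the first statin episode with no risk window after it, so events that follow an illness-prompted stop would be lost in users only

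*SAP*

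**What the plan says.** The as-treated analysis is the first of three listed under Secondary analyses in the SAP. Its aim is "to assess the relationship between continuous statin treatment and outcomes". The rule for doing so reads: "we will apply an as-treated analysis where we further censor the follow-up at the end of the first treatment episode". This adds to the criteria that already end follow-up, which the section Identification of primary and secondary outcomes sets as follows: "Follow-up will begin at index date until the first recorded date of incident CRC, proctocolectomy, emigration, death, or end of follow-up (Dec, 2019"). The same section names the outcomes: "The primary outcome is incident CRC (see Table 2 for ICD codes), while secondary outcomes are CRC-related mortality and all-cause mortality".

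The SAP does not say how the end of an episode is determined. The exposure source is a dispensing register that "collects information on medications dispensed at all pharmacies in Sweden since July 2005, including for example dispensing date, drug name, and a defined daily dose", so an end date has to be constructed from supply. No days'-supply rule, permitted gap or post-episode window is given.

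The main analysis does not use this censoring: "We will use the intention-to-treat analysis as the main analysis".

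The one provision for latency is a sensitivity analysis at the other end of follow-up: "we will discard the first year and then first two years of follow-up from the analysis".

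**The concern.** Censoring at the end of treatment is harmless only if the reason for stopping is unrelated to the outcome. Statins are preventive drugs, and a patient in terminal decline or with early symptoms of cancer may stop them before the death or diagnosis is recorded. The event then falls after the censoring date and disappears, while hardly any person-time goes with it. The Poisson and subdistribution hazard models under Statistical analyses would treat that censoring as uninformative.

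The loss does not cancel between arms, because only users have an episode that can end. It would remain if non-users were censored on starting a statin.

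The direction matters. The SAP's hypothesis is that statin use goes with lower risk of all three outcomes. An as-treated ratio further below 1 than the intention-to-treat ratio would naturally be read as support for continuous treatment, yet it could arise from this censoring alone. The mechanism is most plausible for CRC-related and all-cause mortality, and it can also act on incident CRC.

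**Working it through.** **Plan's own figure.** There is none to reproduce. The SAP states no event rate, stopping rate or as-treated estimate. The check therefore asks what the rule would return if statins had no effect.

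**Inputs from the SAP.** Users are censored at the episode end and non-users are not. Maximum follow-up is July 2006 to December 2019, or 13.5 years.

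**Assumptions not in the SAP.** Event rate λ is 0.002 or 0.02 per year in both arms. Background stopping δ is 0.05 or 0.15 per year. A share q of users' would-be events is preceded by a stop that the coming event prompted. The lead time from stop to event is exponential with mean m of 0.25 or 0.5 year. The episode is taken to end at the stop, so any supply or gap tail would make the effective q smaller.

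**Formula without a window.** A share q of the events is lost. The share of person-time lost is about q·λ·m. Under the null:

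rate ratio ≈ (1 - q) / (1 - q·λ·m)

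For q = 0.3, λ = 0.02 and m = 0.5, the person-time lost is 0.3 × 0.02 × 0.5 = 0.003, and the ratio is 0.700 / 0.997 = 0.702. For λ = 0.002 the person-time lost is 0.0003 and the ratio is 0.700. So the ratio is close to 1 - q and depends little on the event rate or on background stopping.

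**Formula with a window w after the episode end.** A prompted event is still lost only if its lead exceeds w, which has probability exp(-w/m):

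rate ratio ≈ 1 - q·exp(-w/m)

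For q = 0.3 and m = 0.5:

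- w = 0.5: 1 - 0.3 × 0.368 = 0.890
- w = 1: 1 - 0.3 × 0.135 = 0.959

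**Simulation.** Two million people per arm, true ratio 1.00. Each cell gives the lowest and highest ratio over the eight combinations of event rate, stopping rate and mean lead.

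| q | no window | 3 months | 6 months | 12 months |
| --- | --- | --- | --- | --- |
| 0 | 0.994-1.019 | 0.990-1.001 | 0.986-1.003 | 0.990-1.014 |
| 0.1 | 0.897-0.907 | 0.935-0.969 | 0.959-0.988 | 0.982-1.001 |
| 0.3 | 0.699-0.704 | 0.818-0.900 | 0.897-0.963 | 0.955-0.994 |
| 0.5 | 0.494-0.505 | 0.706-0.829 | 0.829-0.939 | 0.932-0.995 |

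The row for q = 0 shows simulation noise only. The other rows agree with the formulas. With a window, some simulated values lie slightly nearer 1, because no event in the first w years after the index date can be lost.

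**Dependence on the lead time.** With a fixed lead of three months (death rate 0.03 per year, stopping 0.10 per year, six years of follow-up), the ratio without a window is 0.901, 0.801 and 0.704 for q = 0.1, 0.2 and 0.3. A six-month window then returns 1.001, 0.999 and 1.000. That full recovery follows from every lead being shorter than the window. With variable leads and q = 0.3, six months leaves 0.90 to 0.96.

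**Other provisions in the SAP.** Dropping the first one or two years acts after the index date, not after stopping. The time-varying covariate model is not described as a model for censoring, nor tied to this analysis. E-values address unmeasured confounding. The fracture control outcome is not linked to the as-treated analysis.

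**The case against.** The strongest reply has four parts.

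1. The register shows when a drug was dispensed, not when the patient stopped taking it. Any workable episode end will include the remaining supply and probably a permitted gap, and that tail is already a partial window. This stands, and it is why q is defined net of the tail. But the tail is not written down, so its length and its protection are unknown.

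2. The ratios restate the assumed share: 0.90 is one minus 0.1. This also stands. The calculation shows the direction and the form of the bias, not its size in this cohort. It uses rate ratios without competing events, whereas the SAP's hazard ratios are subdistribution hazard ratios.

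3. A reader might infer that events which themselves led to stopping are dropped. The SAP does not support that. Follow-up ends at the first recorded CRC or death, so an event recorded on or before the stop date counts. Only an event recorded after a stop that its prodrome prompted (or, for CRC death, that the cancer prompted) is lost.

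4. The intention-to-treat main analysis keeps counting after a stop, up to the ordinary end of follow-up, and a gap between the two analyses would be visible. This limits the damage. But the gap alone would not tell a real effect of continuous use from this artefact.

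**Conclusion.** The point holds for one secondary analysis. As written, the as-treated rule has no post-episode window and no correction for informative censoring, and nothing else in the SAP acts on the time after stopping. If any users stop because of the coming outcome, the comparison with non-users is biased toward protection, by a factor of about 1 - q under the null.

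The SAP supplies no q. The values 0.90 (q = 0.1) and 0.70 (q = 0.3) are therefore illustrations, and at q = 0 the rule is unbiased in this respect. A reader might infer that the analysis must yield hazard ratios below 1 under no effect, or that the primary result is compromised. Neither follows: the first needs q above 0, and the main analysis is intention-to-treat.

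**What to change.** Amend the as-treated paragraph under Secondary analyses in three ways.

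1. Define the episode end from the dispensing data: the days' supply rule and the permitted gap between fills.
2. Keep users at risk, and count their events, for a prespecified window after that date, for example 12 months for CRC and for both mortality outcomes.
3. Repeat with other windows, for example 0, 3, 6 and 24 months. Zero months is the rule as it now stands. Do not describe a 6-month window as removing the bias fully.

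It would also help to report users' events and person-time within the window separately. A raised event rate soon after the episode end would point to illness-prompted stopping. A move of the ratio toward 1 would not by itself, because dilution has the same effect on a protective ratio.

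The cost is a few lines of SAP text and a shifted censoring date. The drawback is dilution, since some untreated time counts as treated. With stopping rate δ and window w, the window makes up at most δw / (1 + δw) of users' person-time. For 12 months this is 0.05 / 1.05 = 5% at 5% stopping per year and 0.15 / 1.15 = 13% at 15% per year (both stopping rates assumed).

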**Two-step matching process**

A two-step matching process will be applied to establish the cohort. In the direct matching step, statin users and non-statin users will be matched on age at IBD diagnosis (<18, 18-<40, 40-<60, and ≥60), sex, IBD subtype (CD or UC), and calendar year at IBD diagnosis (1969-1989, 1990-1999, 2000-2009, 2010-2018). IBD-unclassified will not be considered in this project due to diagnostic uncertainty. To ensure similar opportunities for care and treatment^10^, non-statin users should have a random drug prescription (except IBD medications, see **Table 2** for ATC codes) within three months before or after the start date of statin treatment in the matched statin users. All identified non-statin users will be assigned the same index date as the index statin user. We will exclude individuals who had a record of migration, received a colectomy, or had a diagnosis of any of the following diseases before the index date: cancers, human immunodeficiency virus/ acquired immunodeficiency syndrome, primary immunodeficiency disease, end-stage renal disease, severe liver failure, and any organ transplantation (see **Table 2** for procedure and ICD codes).

In the propensity score matching step, statin users and non-statin users will be matched in a 1:1 ratio by using a greedy nearest-neighbor matching algorithm without replacement, with a caliper of 0.2 standard deviation of the logit of the propensity score^11^. A logistic regression model will be used to calculate the propensity score after adjusting for the below demographic and socioeconomic characteristics, comorbidities, and co-medications identified up to and including the index date.

- Age at IBD diagnosis, years (continuous);
- Duration of IBD, years (continuous);
- Number of healthcare visits (continuous);
- Country of birth (Nordic countries or others);
- Education (0-9, 10-12, ≥13 years, or missing);
- Comorbidities (yes/no, see Table 2 for detail): gastrointestinal diseases, intestinal infections, cardiovascular diseases, obesity/dyslipidemia, type 1 and type 2 diabetes, autoimmune diseases, obstructive sleep apnea, chronic obstructive pulmonary disease, and myositis;
- Medications (yes/no, see Table 2 for detail): antibiotics, proton pump inhibitor, antiviral medications, IBD medications, non-aspirin anti-platelet medications, aspirin, non-statin lipid lowering medications, anti-diabetic medications, anticoagulation medications, and anti-arrhythmias medications.

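### The as-treated analysis adds censoring for statin users only, so comparators who start a statin stay in the untreated arm, and non-use is not tied to the assigned index date

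*SAP*

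**What the plan says.** Statin users are adults "with a statin prescription for ≥30 cumulative DDD (cDDD) from July, 2006 or later" (SAP, Identification of statin users). Their time zero is their own dispensing: "The date that an individual first attained a cDDD ≥ 30 for a statin will be defined as the index date for statin exposure". The new-user exclusion reads "Individuals who had any statin prescription before July 2006, before IBD diagnosis or before the first attainment of cDDD ≥ 30 will be excluded". The same section adds "We will use the intention-to-treat analysis as the main analysis".

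The comparator appears in the section Two-step matching process, where "statin users and non-statin users will be matched on age at IBD diagnosis" and other factors. The group is named but not defined. Its time zero is borrowed: "All identified non-statin users will be assigned the same index date as the index statin user". The exclusions that this section applies before the index date cover migration, colectomy and listed diseases. Prior statin use is not among them.

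The section Identification of primary and secondary outcomes gives the censoring common to both groups: "Follow-up will begin at index date until the first recorded date of incident CRC, proctocolectomy, emigration, death, or end of follow-up (Dec, 2019". Starting a statin is not listed. Under Secondary analyses, the as-treated analysis keeps those criteria and adds one: "we will apply an as-treated analysis where we further censor the follow-up at the end of the first treatment episode".

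**The concern.** An as-treated contrast compares time on treatment with time off treatment, so both arms need a rule for leaving their assigned state. Here users leave when they stop, while non-users have no rule for when they start. The analysis meant to show the effect of continuous treatment then compares on-statin time with a mixture of off-statin and on-statin time.

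The second gap is upstream. The prior-statin exclusion is anchored to July 2006, to IBD diagnosis and to the person's own attainment of 30 cumulative DDD. A non-user never reaches the last anchor, and the assigned index date is not an anchor at all. A programmer could therefore build the comparator from people with no statin up to the index date, or from people with no statin at any time to the end of 2019. The first choice is sound. The second uses information from after time zero to decide who is in the comparison, and would affect the main analysis.

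**Working it through.** The SAP states no figure on this point, so there is nothing to reproduce. All rates below are assumptions, with constant hazards and statin initiation independent of prognosis.

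**1. Which censoring rules reach which arm**

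| Event | Users | Non-users |
|---|---|---|
| CRC, proctocolectomy, emigration, death, Dec 2019 | yes | yes |
| End of first treatment episode (as-treated) | yes | does not exist |
| Starting a statin (as-treated) | not applicable | not stated |

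The one-sidedness concerns only the added treatment-related rule. The other criteria are shared.

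**2. Share of comparator time on statins**, if non-users are fixed at the index date and not censored on starting

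With initiation rate g per year, follow-up T years and no stopping: p = 1 - (1 - exp(-gT)) / (gT).

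- g = 0.01, T = 6: p = 1 - 0.0582/0.06 = 0.029
- g = 0.05, T = 10: p = 1 - 0.3935/0.5 = 0.213

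So p is about 3-21%. At the longest possible follow-up (July 2006 to December 2019, about 13.5 years) and g = 0.05, p = 0.273.

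**3. Effect on the as-treated HR**

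With a true on-treatment HR of 0.75, the observed HR is about 0.75 / (1 - p + 0.75p).

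- p = 0.029: 0.75 / 0.9927 = 0.76
- p = 0.213: 0.75 / 0.9467 = 0.79
- p = 0.273: 0.75 / 0.9318 = 0.80

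A second calculation solved the Cox score equation, with users censored at discontinuation (5% or 20% per year) and non-users never censored on starting, over 6 or 13.5 years. A true HR of 0.70 read 0.71 at 1% initiation per year and 0.73-0.76 at 5%. Censoring non-users at their first dispensing returns 0.70.

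**4. If non-user were applied as never-user: death**

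Take a true null, event rate l, initiation rate g, k = l + g and horizon A. Among people who do not start before the end of their own follow-up:

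- events per person = (l/k)(1 - exp(-kA))
- person-years per person = l(1 - exp(-kA)(1 + kA))/k² + A exp(-kA)

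For death at 30 per 1000 person-years:

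- g = 0.05, A = 10: events 0.2065, person-years 5.390, rate 0.0383, spurious ratio 0.03/0.0383 = 0.78
- g = 0.01, A = 6: events 0.1600, person-years 5.181, rate 0.0309, spurious ratio 0.97

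**5. If non-user were applied as never-user to 2019: CRC**

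CRC does not end the chance of starting a statin, so cases who start afterwards are also removed. If initiation is unrelated to CRC and nobody dies, not starting by a fixed date carries no information about CRC, and the ratio is 1.00. Simulation with CRC at 2 per 1000 person-years, a true null, 1-5% initiation per year and 6-10 years gave:

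| Assumption | Spurious ratio |
|---|---|
| No deaths, same initiation after CRC | 1.00 |
| Mortality 3%/year before and 10%/year after CRC, same initiation | 0.95-1.00 |
| Same mortality, initiation halved after CRC | 0.87-0.98 |
| Same mortality, no initiation after CRC | 0.78-0.97 |

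Defining non-use at the index date removes this selection and returns the null ratio to 1.00.

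**The case against.** The strongest reply is that the SAP never says never-user. It calls the main analysis intention-to-treat, gives comparators the matched user's index date, requires another dispensing within three months of that date, and takes covariates only up to it. The July 2006 phrase is a calendar bound on users' dispensings, not evidence that comparator status looks ahead. All of this stands. A reader might infer that the primary HR is biased as planned, but the documents do not support that. They leave the possibility open and lean against it.

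A reader might also apply the mortality-type range in step 4 to the primary outcome. It carries over to CRC only if non-use is judged to the end of the person's own follow-up, or if no case ever starts a statin after CRC. Otherwise the bias is smaller and can vanish, as step 5 shows.

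A third tempting inference is that users stop because they are falling ill, so their events are censored away and a protective effect appears. That is plausible, but nothing in the SAP says how often it happens, so no size can be given.

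Finally, the as-treated analysis is secondary, the dilution is toward the null, and the nested case-control analysis by cumulative duration needs no non-user comparator. This limits the consequence but does not supply the missing rule. The listed sensitivity analyses do not supply it either: dropping early follow-up and adjusting for time-varying covariates leave a comparator's later statin use uncensored.

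**Conclusion.** The point holds in two parts of different standing.

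- **As-treated analysis.** Followed as written, it keeps statin-treated time in the untreated arm. The bias is toward 1 and small to modest: a true 0.75 reads about 0.76-0.79 if non-users start at 1-5% per year over 6-10 years and do not stop. It affects one secondary analysis. With non-use fixed at the index date, the main analysis is unaffected.
- **Definition of non-user.** This is an omission, not a stated error. If it were resolved as never-use, the comparison would favour statins, the direction of the study hypothesis. For all-cause mortality at 30 per 1000 person-years, a true null would read 0.97-0.78 under the same initiation rates and follow-up. For CRC the size depends on statin initiation and death after CRC and may be nil.

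All sizes rest on assumed rates. The change should be made because the comparator definition and the censoring rules are the SAP's own subject, and each gap closes with a sentence.

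**What to change.** 1. In Two-step matching process, define a non-user as a person with no statin dispensing up to and including the assigned index date, regardless of later use. State that this assignment is kept in the main analysis, and whether a later starter may also enter as a user.
2. In Secondary analyses, state that the as-treated analysis also censors non-users at their first statin dispensing.
3. Optionally, as a sensitivity check, repeat the as-treated analysis with inverse-probability-of-censoring weights built from the covariates already collected, because stopping or starting may be related to prognosis. The first two changes remove only the mechanical bias.

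The cost is SAP wording, some re-programming of the comparator pool and slightly less comparator follow-up in a secondary analysis. If a person can contribute to both groups, a robust variance is needed.

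### The nested case-control analysis names incidence density sampling but bars future cases as controls and sets no reference date for counting controls' statin use; under one reading this gives a false protective duration trend

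*SAP*

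**What the plan says.** The second of the three analyses under Secondary analyses is a nested case-control study within statin users, meant to show whether longer use goes with fewer outcomes. Its rules are:

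- Method: "Using the method of incidence density sampling, for each case exposed to statin and with later studied outcomes".
- Controls: "we will randomly select up to five statin users who did not develop the interested outcomes (controls". Nothing limits this to being outcome-free by the case's date.
- Matching: "They will be individually matched on age at index date, gender, IBD subtype, IBD duration, and duration of follow-up". No tolerance is given. The SAP does not say whether the last factor means total follow-up or a minimum.
- Exposure window: "The cumulative duration of statin use will be assessed between first prescription and end of follow-up".
- Strata: "30 days-<1 year (reference group), 1-<2 years, 2-<5 years, and ≥5 years cDDD".
- Model: "Conditional logistic regression will be used to estimate odds ratios (ORs) with 95% CIs", with a trend test across the strata.

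The section on primary and secondary outcomes ends each person's follow-up at the first of CRC, proctocolectomy, emigration, death or December 2019. Statin users enter from July 2006, so follow-up can last about 13.5 years. No reference date for controls appears anywhere in the SAP.

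**The concern.** There are two separate faults in the text.

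First, incidence density sampling draws controls from everyone under observation and outcome-free at the moment the case occurs. Someone who becomes a case later belongs in that pool. Restricting controls to people who never have the outcome describes a different design.

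Second, a case's follow-up ends at the event, but a control who was at risk at that moment may be followed for years more. If each person's use is summed to their own end of follow-up, controls have more time in which to reach the longer strata. Whether this happens depends on what the follow-up matching means, and the SAP does not say.

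This is the plan's only duration-response analysis and its only trend test. An artefact from longer windows in controls would point towards protection, the direction of the SAP's hypothesis, and so could be read as confirmation.

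**Working it through.** **No figure to reproduce.** The SAP gives no event count, power or expected odds ratio for this analysis. The check is an argument on direction, then a simulation for size.

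**Direction.** Let x(t) be cumulative statin use by time t since index. With risk-set sampling and conditional logistic regression, a case i at time t contributes exp(βx_i(t)) / Σ exp(βx_j(t)). The sum runs over the case and its controls, and every x is taken at the same t. If control j is instead counted to its own end T_j ≥ t, x_j(t) is replaced by x_j(T_j). Cumulative use cannot fall, so x_j(T_j) ≥ x_j(t). Controls can move only to longer strata while the case stays where it is, which pushes the odds ratio for long use below its true value. If T_j = t, nothing moves.

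**Size under the null.** Statin duration was given no effect, so the true odds ratio is 1. From the SAP: up to five controls per case, the four duration strata, conditional logistic regression, and a maximum of 13.5 years (July 2006 to December 2019). The SAP does not give the following, so they are assumptions:

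- uniform entry over the 13.5 years;
- CRC as outcome at 1.5 per 1,000 person-years, with death at 20 per 1,000;
- death as outcome at 10, 20 or 40 per 1,000;
- other censoring at 5 per 1,000;
- stopping of statins at 0.05, 0.1 or 0.3 per year for CRC and 0.1 for death;
- stopping and censoring independent of outcome.

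Each scenario used 12,000 cases. Odds ratios for at least 5 years against under 1 year, as ranges over the scenarios:

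| Reading of the plan | CRC | Death |
| --- | --- | --- |
| Risk-set controls, use to the case's date | 1.00–1.07 | 0.98–1.06 |
| At-risk controls, never cases, use to own end | 0.10–0.32 | 0.17–0.19 |
| At-risk controls, later cases eligible, use to own end | 0.10–0.33 | 0.17–0.19 |
| No follow-up matching, never cases, use to own end | 0.46–0.59 | 0.45–0.49 |

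Two further readings, over both outcomes together:

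- At-risk controls who are never cases, use cut at the case's date: 0.97 to 1.06.
- Never-case controls matched on total follow-up within 0.5 or 0.1 year, use to own end: 0.96 to 1.07.

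Taking CRC with stopping at 0.1 per year as an example, never-case controls at risk and counted to their own end give:

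- 1 to <2 years: 0.77 (95% interval 0.72–0.83)
- 2 to <5 years: 0.51 (0.49–0.54)
- at least 5 years: 0.18 (0.17–0.19)
- trend: 0.57 per stratum

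Risk-set controls with use cut at the case's date give 0.97, 0.97 and 1.00 (0.92–1.10 for the last), with a trend of 1.00.

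A second null simulation assumed CRC at 3 and death at 30 per 1,000 person-years and a mean of 6 years on statin. It gave 0.82, 0.58 and 0.24 with use to own end, against 1.02, 1.01 and 1.00 with use cut at the case's date.

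**Which fault drives the trend.** Making later cases eligible while keeping the unequal window leaves the bias unchanged (0.10–0.33 against 0.10–0.32 for CRC). Cutting use at the case's date while keeping never-case controls removes it. The window is the cause, not the exclusion of future cases.

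**The case against.** The best defence is that the intended design may already be correct. "Using the method of incidence density sampling" is a standard term. A programmer who follows it might give each control the case's date unprompted and read the control definition as outcome-free so far. Matching on follow-up duration could itself make the windows equal, and the null simulation then shows no trend. The analysis is also one of three secondary ones, confined to statin users.

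Much of this stands, and it limits what can be claimed. It does not remove the fault, because nothing in the SAP requires the favourable reading.

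Four stronger readings go further than the document supports:

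- A reader might infer that the plan will produce a false protective trend. The text allows that reading but does not state it; the result depends on an undefined matching factor.
- A reader might infer that excluding future cases creates the trend. It contradicts the named method, but alone it produced no null trend. It could move the odds ratio away from the rate ratio when an effect exists and the outcome is common, such as death. No size for this is claimed here: a simple cumulative odds ratio formula does not describe a time-matched design.
- A reader might infer that matching on equal total follow-up is also biased, since such controls are people leaving observation at that time. The simulation shows no bias under independence. Stopping or censoring related to outcome could change that, but the SAP gives nothing from which to judge it.
- A reader might infer that the main results are affected. The primary CRC analysis and the main mortality analyses do not use this sampling.

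**Conclusion.** The concern holds as a contradiction and an omission. The control definition conflicts with incidence density sampling, controls have no reference date, and the follow-up matching has two readings with very different consequences.

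If it means at risk at least as long as the case, with use counted to each person's own end, the null odds ratio for at least 5 years against under 1 year is about 0.1 to 0.3. If total follow-up is closely equal, or use is cut at the case's date, it is about 1 (0.96 to 1.07).

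The size rests on assumed event, stopping and censoring rates; the direction under the unequal window did not change over the ranges tried. The near-null results rest on stopping and censoring being independent of outcome. This should be fixed because it is the plan's only duration-response evidence. It does not threaten the primary estimate.

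**What to change.** Rewrite the sampling and exposure sentences under Secondary analyses to state that:

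1. For each case at time t since index, up to five statin users are sampled who are under observation and outcome-free at t, including users who become cases later.
2. Those controls take t as their reference date.
3. Statin use is summed from first prescription to t, for the case and its controls alike.
4. The follow-up matching factor is replaced by being at risk at the same time since index. The other matching factors stay.

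The cost is a few sentences and a small change to the sampling program, with no new data. If the analysis has already been run, report which control definition and exposure window were used, and rerun it if use was counted past the case's date.
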